# SYNOPSIS

| Protocol Title: | **Role of IL-1** **in the regulation of muscle derived IL-6 during exercise** |
| --- | --- |
| Sponsor/Investigator: | [name], Professor, Division of Endocrinology, Diabetes and Metabolism Department of Internal Medicine  University Hospital Basel, Switzerland |
| Protocol Number: | 10.0 |
| Amendment | 1 |
| Study Phase: | 2 |
| Study Drug: | Anakinra (Kineret) and Placebo |
| Study Population: | Healthy lean males |
| Objective: | Evaluate the regulation of muscle derived IL-6 during exercise and in particular whether it is regulated by the IL-1 system. |
| Program Hypothesis: | Muscle derived IL-6 is regulated by IL-1 vs. independently of the IL-1 system during an acute exercise bout |
| Study Design: | Placebo-controlled, double blind, cross-over, randomized, proof-of-concept |
| Sample Size: | 20 subjects |
| Estimated Start: | July, 2011 |
| Estimated Finish: | December, 2011 |
| No. of Sites: | 1 |
| Mean Study Duration for Subjects: | 36d  (screening visit included) |
| Eligibility Criteria: | Inclusion Criteria  Subjects may be included in the study if they meet all of the following criteria:   - male - non-smoking - apparently healthy - BMI >18 and <26kg/m2 - Age 20-50 years - Regular exercise including a minimum of two runs weekly of a total duration of > 2h - Willingness to use contraceptive measures adequate to prevent the subject’s partner from becoming pregnant during the study. Adequate contraceptive measures include hormonal methods used for two or more cycles prior to screening (e.g., oral contraceptive pills, contraceptive patch, or contraceptive vaginal ring), double barrier methods (e.g., contraceptive sponge, diaphragm used in conjunction with contraceptive foam or jelly, and condom used in conjunction with contraceptive foam or jelly), intrauterine methods (IUD), sterilization (e.g., tubal ligation or a monogamous relationship with a vasectomized partner), and abstinence. |
|  | Exclusion Criteria  Subjects will be excluded from the study if they meet any of the following criteria:   - Clinical signs of infection in the week before inclusion or history of infection during the last 3 months (CRP >5mg/l) - Impaired fasting glucose (fasting plasma glucose >5.5mmol/l) - Hematologic disease (leukocyte count < 1.5x109/l, hemoglobin <11 g/dl, platelets <100 x 103/ul) - Kidney disease (creatinine > 1.5 mg/dL for men and 1.4mg/dL for woman) - Liver disease (transaminases >2x upper normal range) - Heart disease - Pulmonary disease - Inflammatory disease - History of carcinoma - History of tuberculosis - Alcohol consumption >40g/d - Known allergy to Kineret - Current treatment with any drug in the week before inclusion, including vitamin supplementation (especially vitamin C and E) - Use of any investigational drug within 30 days prior to enrollment or within 5 half-lives of the investigational drug, whichever is longer - Subject refusing or unable to give written informed consent |
| Endpoints/ Outcome Measures: | ***Primary***:  The primary endpoint is change in exercise-stimulated IL-6 between group dosed with placebo and anakinra  Secondary:   - Change in glucose metabolism, insulin, glucagon and GLP-1 secretion due to any treatment. - Change of inflammatory markers (CRP, TNFα, IL-1Ra) due to any treatment. - Change of stress hormones (cortisol, growth hormone) due to any treatment. - Change of muscular enzymes (CK) due to any treatment. - Well-being during and after exercise including muscle soreness due to any treatment. - Activity Induced Fatigue (ACTIF) Scale before and after exercise - Depression - Cognition - Motor strength - Change of vascular function (CAVI, PWV and AVR) due to any treatment. |
| Safety Evaluations: | All recommendations outlined in the ICH Guidelines for Good Clinical Practice will be adhered to throughout this trial. The safety of the drug will be assessed by multiple subject assessments of vital signs, physical exams, clinical tests, and laboratory evaluations, and monitoring of adverse events (AEs). Concomitant medications will be assessed. |
| Biological Evaluations: | The following tests will be used to investigate how IL-6 is regulated (see Appendix 2 for time points):   - IL-6 - GLP -1 (active) - GIP - Glucagon - Insulin - Glucose - IL-1Ra - CRP - TNF-α - Cortisol - GH - CK |
| Sample Size: | The sample size (20 subjects) was based on clinical and practical considerations. |
| Statistical Considerations: | Subject demographics, medical history, and prior medications will be summarized by treatment group using descriptive statistics. All randomized subjects who receive at least one study treatment will be considered for analysis. Endpoints will be summarized descriptively and graphically by treatment and study visit. |

Appendix 12 Activity questionnaire (Aktivitätsfragebogen)………………………………….64

LIST OF ABBREVIATIONS

| ACTIF Scale | Activity Induced Fatigue Scale |
| --- | --- |
| ADCC | Antibody dependent cell-mediated cytotoxicity |
| AE | Adverse event |
| ALT | Alanine aminotransferase |
| ANC | Absolute neutrophil count |
| ANCOVA | Analysis of covariance |
| AST | Aspartate aminotransferase |
| ATC | Acute toxic class (of WHODRUG dictionary) |
| AUC | Area under the curve |
| AVR | Arteriolar-to-venular-ratio |
| BDI-FS | Beck-Depression-Inventory Fast Screen |
| BMI | Body mass index |
| BP | Blood pressure |
| BUN | Blood urea nitrogen |
| CAVI | Cardio-ankle vascular index |
| CBC | Complete blood count |
| CHO | Chinese hamster ovary |
| CRF | Case Report Form |
| CTCAE | Common Terminology Criteria for Adverse Events |
| EC | Ethics Committee |
| ECG | Electrocardiogram |
| ECL | Electrochemiluminescence |
| GCP | Good Clinical Practice |
| GIP | Gastric inhibitory polypeptide |
| GLP | Good Laboratory Practice |
| GLP-1 | Glucagon-like peptide-1 |
| HbA1c | Test measuring the amount of glycosylated hemoglobin in blood |
| HDL | High-density lipoprotein |
| hs-CRP | High sensitivity C-reactive protein |
| ICH | International Conference on Harmonization |
| IL-1 | Interleukin-1 |
| IV | Intravenous |
| LDL | Low-density lipoprotein |
| mAb | Monoclonal antibody |
| MedDRA | Medical Dictionary for Regulatory Activities |
| MHC | Major histocompatibility complex |
| NCI | National Cancer Institute |
| NOAEL | No-observed-adverse-effect-level |
| NSAID | Non-steroidal anti-inflammatory drug |
| PD | Pharmacodynamic |
| PK | Pharmacokinetic |
| PWV | Pulse wave velocity |
| rHu | Recombinant human |
| rMu | Recombinant mouse |
| SAE | Serious adverse event |
| SC | Subcutaneous |
| SDMT | Symbol Digit Modalities Test |
| SNF | Swiss National Foundation |
| siRNA | Small interfering RNA |
| TLR | Toll-like receptor |
| T1D | Type 1 diabetes |
| T2D | Type 2 diabetes |
| USP | United States Pharmacopeia |
| ULN | Upper limit of normal |
| VAS | Visual analogue scale |
| WBC | White blood cell (count) |
| WHO DRUG | World Health Organization Drug Dictionary |

# 1.0 background

## 1.1 Overview

The role of IL-6 in regulating glucose homeostasis is unclear and the ongoing debate is characterized by IL-6 being a “bad or a good guy”. In support of the bad guy hypothesis systemic IL-6 levels are elevated in obese individuals and in patients with type 2 diabetes, and these elevated IL-6 levels predict disease development (1; 2). In addition, IL-6 induces insulin resistance in liver and fat tissues (3). The discovery that skeletal muscle produces and releases IL-6 in response to muscle contraction (exercise) has challenged the bad guy hypothesis, in addition, the fact that IL-6 improves muscle insulin sensitivity (3) supports a potential beneficial role of IL-6 in regulating glucose homeostasis. We have recently observed that IL-6 induces GLP-1 production and release from intestinal L-cells and islet -cells (Ellingsgaard et al., manuscript in preparation), indicating that IL-6 may play an important beneficial role in regulating glucose homeostasis.

It has been shown recently that IL-1 antagonism improves glycemia and insulin secretion in patients with type 2 diabetes (4). However, IL-1 antagonism also decreases IL-6 levels in auto-inflammatory diseases including type 2 diabetes. Subsequently, IL-1 antagonism could possibly decrease GLP-1 levels and thereby reduce the beneficial effect of IL-1 antagonism on glucose-metabolism.

Exercise improves -cell function but the underlying mechanism is unclear. Since muscle contraction leads to a strong increase in circulating IL-6 (5), we hypothesize that exercise-induced IL-6 promotes GLP-1 secretion from intestinal L-cells and islet α-cells, thereby providing a mechanism how physical activity (exercise) can help maintain and improve -cell function in obese individuals and patients with type 2 diabetes.

However, little is known about the regulation of muscle derived IL-6 during exercise and in particular whether it is regulated by IL-1 or independently of the IL-1 system. The presence of high levels of IL-1α in the muscle makes it a candidate for IL-6 regulation.

[http://www.informaworld.com/smpp/title~db=all~content=t713926139~tab=issueslist~branches=18 - v18](http://www.informaworld.com/smpp/title~db=all~content=t713926139~tab=issueslist~branches=18" \l "v18)Evidence is growing that an increase in inflammatory markers is directly linked with fatigue (6). IL-6 is crossing the blood-brain barrier and has been described to be associated with increased fatigue after training overload (7). Hypothesizing that IL-1 antagonism will decrease IL-6 we intend to investigate the effect of IL-1 antagonism on fatigue after exercise.

Pedersen et al. showed that skeletal muscle produces IL-6 in response to physical activity (5). IL-6 has been demonstrated to be directly involved in stress-induced hypertension (8) as well as angiotensin-II mediated hypertension (9). Hypothesizing that IL-1 antagonism will decrease IL-6 we intend to investigate the effect of IL-1 antagonism on vascular function after exercise.

## 1.2 Disease Pathophysiology

We will be evaluating the normal physiology of skeletal muscle in an exercise setting.

## 1.3 Clinical Data

A recently completed 13-week clinical study of anakinra therapy in type 2 diabetes (T2D) was based on the rationale that in vitro glucotoxicity to human β-cells can be prevented with IL-1Ra, and that glucose induces islet IL-1 production, which causes β-cell apoptosis and impaired function by pathways partly similar to those suspected to operate in T1D diabetes (4). This study provided proof-of-principle that inhibition of IL-1 signaling can improve glycemia and β-cell function. Interestingly, the maximal effect on glycemia with anakinra was seen after 4 weeks and fasting blood glucose already was significantly reduced after 1 week, suggesting rapid effects on β‑cell secretory capacity rather than changes in b‑cell mass. Long-term treatment may uncover additional beneficial effects on b‑cell mass.

## 1.4 Anakinra/Kineret®

Kineret (anakinra; r-metHuIL-1ra, Amgen Inc.) is a recombinant, nonglycoslyated form of the human interleukin-1 receptor antagonist (IL-1Ra) in a 100 mg/ml solution for s.c. injection. Kineret differs from native human IL-1Ra in that it has the addition of a single

methionine residue at its amino terminus. Kineret consists of 153 amino acids and has a molecular weight of 17.3 kilodaltons. Kineret is produced by recombinant DNA technology using an E. coli bacterial expression system.

Mild and transient injection reactions occurring in 20-50% of subjects may pose a problem in maintaining the blinding of the study, but is a similar problem in many trials using drugs with easily recognizable side-effects e.g. cyclosporine, PPARγ agonists and GLP-1. There is no alternative than to strive for the best masking possible since it is not ethically defendable to add drugs, e.g. histamine to placebo to reproduce the local adverse effects of anti-IL-1. Since only one fifth to one half of patients develops local reactions to anakinra, patients NOT developing those reactions cannot exclude that they receive active drug.

Anakinra is FDA approved for the indication rheumatoid arthritis (10,11) and has an acceptable risk / benefit profile in this indication, with more than 100.000 patients treated. Most common adverse events include mild and transient local injection reactions in 20-50% of subjects treated with Anakinra. Consistent with its mechanism of action, anakinra reduces WBC/ANC in 2.4% of patients and this may increase the risk of infection. Accordingly, treatment with anakinra will not be initiated in patients with active infections. Safety will be monitored by physical exams and blood and urine tests. Additional information is provided in the Investigator’s Brochure.

## 1.5 Study Rationale

The aim of the study is to investigate whether exercise induced increases in IL-6 are dependent on the IL-1 system. In addition, we will assess the effect of IL-1 antagonism on insulin and GLP-1 secretion as well as muscle soreness,fatigue and vascular function in response to an acute exercise bout.

Since IL-1 antagonism improves glycemia and insulin secretion in patients with type 2 diabetes it is important to investigate if in parallel to this beneficial effect it has an impact on muscle derived IL-6 with subsequent decrease in GLP-1. This may require additional medication like IL-6 substitution or DPP-IV antagonists.

# 2.0 OBJECTIVES

The primary objective of this study is to assess the regulation of muscle derived IL-6 during exercise and in particular whether it is regulated by the IL-1 system.

# 3.0 Study Design

## 3.1 Description of the Study

This is a randomized placebo-controlled, double blind, cross-over, proof-of-concept study of the effects of IL-1 antagonism on peripheral muscle physiology.

The study will consist of one screening visit followed by 3 study visits. During the first two study visits, the subjects (20 apparently healthy, lean men) will perform a submaximal exercise bout on a treadmill for 60 minutes. In addition, subjects will fill in an Activity Induced Fatigue (ACTIF) Scale before (ACTIF pre) and 3-4 hours after (ACTIF post) exercise. After every ACTIF Scale evaluation the subjects perform a Hand-Grip-Strength-Test, assessing the actual motoric shape. Then the subjects are tested by a neuropsychologist by applying the Symbol Digit Modalities test (SDMT), a cognitive screening-test to assess information processing speed and working memory. To assess depression, subjects will be examed by the Beck-Depression-Inventory Fast Screen (BDI-FS), a short version of the Beck-Depression-Inventory (BDI), depicting different facets of depression. These additional tests are performed to evaluate the impact of fatigue on cognitive, motoric and emotional behavior. Before the Activity Induced Fatigue (ACTIF) Scale after exercise (ACTIF post) is applied, subjects will be asked to evaluate their general, motoric and cognitive condition using the Visual analogue scale (VAS) Fatigue after exercise. Subjects will be randomly assigned into two groups consisting each of 10 subjects receiving study medication in a double-blinded, crossed over manner. Treatment consists of a single subcutaneous injection of 100mg IL-1Ra or placebo at visit 1 and 2.,

[visit 1: IL-1Ra/ placebo; visit 2: placebo/ IL-1Ra (cross-over to day 1);]. See table 1 on page 18.

Additionally the vascular function will be evaluated before the injection of the study medication and 1 hour after the exercise bout. The large arterial stiffness known as cardio ankle vascular index (CAVI) and the pulse wave velocity (PWV) will be measured by an oscillometric sphygmograph (Vasera). Furthermore the small vessels will be examined by taking a picture from the retina to calculate the arteriolar-to-venular-ratio (AVR). To assess overall activity of the participants will be given an activity questionnaire (Aktivitätsfragebogen) at screening (12).

The screening visit and the three study visits will be separated by at least 72 hours and at most 9 days.

.

## 3.2 Rationale for Study Design and Dose Level

### 3.2.1 Rationale for Dose Level

#### **3.2.1.1 Anakinra/Kineret®**

The standard dose of anakinra is 100 mg, without adjustment for body weight. For a more complete discussion, please refer to the current Investigator’s Brochure.

### 3.2.2 Rationale for Study Design

The 20 subjects in this study will receive SC doses of 100 mg anakinra or placebo. The size of the active and placebo groups are considered adequate for an exploratory appraisal of the effects of treatment with anakinra on peripheral muscle physiology.

## 3.3 Selection of Study Population

### 3.3.1 Subject Recruitment

Subjects will be recruited from the local population by internet ([www.endo-diabasel.ch](http://www.endo-diabasel.ch/), [www.markt.unibas.ch](http://www.markt.unibas.ch/)) and newspaper advertisement (Baslerstab, 20Minuten). Subjects responding to the advertisement will be screened by a telephone interview. Those deemed eligible will be invited for a screening visit.

### 3.3.2 Inclusion Criteria

Subjects may be included in the study if they meet all of the following criteria:

- male
- non-smoking
- apparently healthy
- BMI >18 and <26kg/m2
- Age 20-50 years
- Regular exercise including a minimum of two runs weekly of a total duration of > 2h
- Willingness to use contraceptive measures adequate to prevent the subject’s partner from becoming pregnant during the study. Adequate contraceptive measures include hormonal methods used for two or more cycles prior to Screening (e.g., oral contraceptive pills, contraceptive patch, or contraceptive vaginal ring), double barrier methods (e.g., contraceptive sponge, diaphragm used in conjunction with contraceptive foam or jelly, and condom used in conjunction with contraceptive foam or jelly), intrauterine methods (IUD), sterilization (e.g., tubal ligation or a monogamous relationship with a vasectomized partner), and abstinence.

### 3.3.3 Exclusion Criteria

Subjects will be excluded from the study if they meet any of the following criteria:

- Clinical signs of infection in the week before inclusion or history of infection during the last 3 months (CRP >5mg/L)
- Impaired fasting glucose (fasting plasma glucose >5.5mmol/L)
- Hematologic disease (leukocyte count < 1.5x109/L, hemoglobin <11 g/dL, platelets <100 x 103/uL)
- Kidney disease (creatinine > 1.5 mg/dL for men and 1.4mg/dL for woman)
- Liver disease (transaminases >2x upper normal range)
- Heart disease
- Pulmonary disease
- Inflammatory disease
- History of carcinoma
- History of tuberculosis
- Alcohol consumption >40g/d
- Known allergy to Kineret
- Current treatment with any drug in the week before inclusion, including vitamin supplementation (especially vitamin C and E)
- Use of any investigational drug within 30 days prior to enrollment or within 5 half-lives of the investigational drug, whichever is longer
- Subject refusing or unable to give written informed consent

## 3.4 Prior and Concomitant Therapy

Concomitant medications are prohibited during the specified time periods:

## 3.5 Enrollment, Treatment Assignment, Blinding, and Unblinding

### 3.5.1 Enrollment

Once Screening is completed and subject eligibility is confirmed, a subject will be assigned a subject number and a kit number(s) according to the randomization schedule.Enrolled subjects who discontinue the trial prior to receiving study drug will be replaced. Subjects who discontinue after receiving any amount of study drug will not be replaced (see Section 4.3.1).

### 3.5.2 Treatment Assignment

Subjects who meet the study eligibility requirements and have signed the informed consent will be randomly assigned to receive study medication according to the following chart:

Table 1
Study design

|  | **1** | **2** |
| --- | --- | --- |
| 20 Participants | Group 1: (n=10)  **IL-1Ra** | Group 1: (n=10)  **Placebo** |
| Group 2: (n=10)  **Placebo** | Group 2: (n=10)  **IL-1Ra** |

### 3.5.3 Treatment Blinding

This is a blinded study in which the subject, as well as the principal investigator, study coordinator, and other site personnel will have no knowledge of subject treatment assignments for the duration of the trial. The study is being blinded in this way to prevent bias in the safety evaluation, in particular the severity grading and causality determinations for AEs. The pharmacist may become unblinded during visual inspection of study drug. After all subjects have completed Final Visit assessments, the data will be cleaned and locked, and personnel will be unblinded in order to complete analysis of data. The clinical Trial Unit (CTU) of the University Hospital Basel, Switzerland, will be responsible for treatment blinding and preparation of trial drugs throughout the study.

All active and placebo vials will be randomized with a kit number. Subjects will be assigned a unique subject number and kit number (or kit numbers if they require multiple vials) according to the randomization schedule. The label on the vial will indicate the study number and kit number but will not indicate the treatment assignment. Subject number will be filled in on the label upon randomization.

After preparation the color, consistency and amount of Verum/Placebo (on visits 1 and 2) will be indistinguishable.

The randomization schedule will be kept by an independent outside biostatistician, as well as the company responsible for packaging, labeling, distribution of the vials, and assignment of kits to subjects.

The investigator must contact the CTU if it is necessary to break the blind (see Section 3.5.4).

### 3.5.4 Treatment Unblinding

Unblinding of individual treatment assignment will occur when medically necessary.

## 3.6 Treatment

### 3.6.1 Formulation of Anakinra/Kineret®

Anakinra will be commercially acquired. The matching placebo for Anakinra will be saline (NaCl 0.9%).

The composition of the Anakinra drug product formulation is provided in Table 2

Table 2
Composition of Drug Product
(100mg Formulation)

| Ingredient | Concentration |
| --- | --- |
| r-metHuIL-1ra (Anakinra) | 150mg/mL |
| Natriumcitrat |  |
| Natriumchlorid |  |
| Natriumedetat |  |
| Polysorbat 80 |  |
| Natriumhydroxid |  |
| Wasser für Injektionszwecke |  |

For further details on the formulation of Anakinra/Kineret®, see the Investigator’s Brochure.

### 3.6.2 Labeling

All vial labels will include the information specified in Figure 1 (on visits 1 and 2) .

Figure 1
Anakinra/Placebo Sample Study Drug Vial Label

| *Protokoll-Nr.:* 9.0 **Anakinra oder Placebo für Anakinra**  Inhalt: 1  1.0 ml | | | | | | |
| --- | --- | --- | --- | --- | --- | --- |
|  | Steriles Lösung für subkutanen Gebrauch Dosierung und Verabreichung: 1.0ml s.c. | | | | |  |
| Probanden-ID:  _________ | | | Chargen-Nr.: JXXXX | *Zubereitet durch / Datum:*  ______________ | | |
| Überprüfungstermin: xx/xx Lagerung bei: 2 – 8°C (36 – 46°F) | | | | | | |
| VORSicht Nur zur Verwendung in der klinischen Studie | | | | | | |
|  | | **Sponsor:**  [name], UniversitätsSpital Basel, [name], Schweiz, [name] | | |  | |

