### 3.6.4 Dosage, Preparation, Administration, and Storage

#### 3.6.4.1 Dosage

Each subject will receive one SC injections of study drug (100 mg anakinra or matching placebo) on visits 1, 2

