Blood samples will be centrifuged and the plasma stored at -80C prior to being assayed.

The following procedures and assessments will be conducted pre-dose unless otherwise indicated:

- Interim medical history
- Concomitant medications
- Vital signs including pulse, blood pressure (systolic/diastolic), respiratory rate, temperature (oral or tympanic), p02, and body weight. Weight is measured pre-dose to calculate the study drug dose to be administered throughout the study. All vital signs other than weight are recorded within 15 minutes prior to the injection, every 30  10 minutes following the injection until 2 hours after the injection, and immediately prior to the subject’s release. Subjects will not be discharged from the facility on Day 0 until at least 2 hours after the injection and at least 1 hour after vital signs are stable. If a subject experiences an SAE, vital signs may be taken more frequently, per standard institutional practice.
- Activity Induced Fatigue Scale ACTIF pre
- SDMT
- BDI-FS
- Hand-Grip-Strenth-Test
- Retrospective analysis blood sample
- First blood sample
- Study drug administration
- Exercise bout (post-dose)
- AEs (post-dose)

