
After all procedures for this visit have been completed, subjects should resume medications as previously prescribed.

All exercise will be carried out with a heart rate monitor in order to document and control exercise intensity.

Blood samples will be centrifuged and the plasma stored at -80C prior to being assayed.

The following procedures and assessments will be conducted pre-dose, unless otherwise indicated:

- AEs (pre-and post‑dose)
- Concomitant medications
- Muscle soreness
- Vital signs including pulse, blood pressure (systolic/diastolic), respiratory rate, temperature (oral or tympanic), p02, and body weight. Weight is measured pre-dose. All vital signs other than weight are recorded within 15 minutes prior to the injection, every 30  10 minutes following the injection until 1 hour after the injection, and immediately prior to the subject’s release. Subjects will not be discharged from the facility until at least 3 hour after the injection. If a subject experiences an SAE, vital signs may be taken more frequently, per standard institutional practice.
- Activity Induced Fatigue Scale ACTIF pre
- SDMT
- BDI-FS
- Hand-Grip-Strength-Test
- Retrospective analysis blood sample
- First blood sample
- Study drug administration
- Exercise bout (post-dose)
- AEs (post-dose)

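### The protocol gives two concentrations for the same anakinra product and no preparation step linking them to the labelled 1.0 ml and the 100 mg dose; one sentence also ties the dose to body weight

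*Protocol*

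**What the plan says.** All of the statements are in the protocol.

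- **Concentration, section 1.4:** the product is described as supplied "in a 100 mg/ml solution for s.c. injection".
- **Concentration, section 3.6.1, Table 2:** the composition table, headed as the 100 mg formulation, lists "r-metHuIL-1ra (Anakinra) | 150mg/mL".
- **Volume, section 3.6.2, Figure 1:** the sample vial label, in German, gives dosage and administration as "Dosierung und Verabreichung: 1.0ml s.c". The same label serves anakinra and placebo.
- **Dose, section 3.6.4.1:** "Each subject will receive one SC injections of study drug (100 mg anakinra or matching placebo) on visits 1, 2". The same 100 mg appears in sections 3.1, 3.2.2, 3.7, 4.2.2.1 and 4.2.2.2 and in Appendix 3.
- **Preparation, section 3.6.4.2:** a single sentence says who prepares the drug and that this happens before administration. It gives no diluent, dilution step or volume to withdraw.
- **Weight, section 3.2.1.1:** "The standard dose of anakinra is 100 mg, without adjustment for body weight".
- **Weight, section 4.2.2.1, vital signs at Visit 1:** "Weight is measured pre-dose to calculate the study drug dose to be administered throughout the study". The matching text for Visit 2 in section 4.2.2.2 mentions no dose calculation: "Weight is measured pre-dose. All vital signs other than weight are recorded within 15 minutes prior to the injection".

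**The concern.** Concentration times volume should return the stated dose. Here it does so with one of the two concentrations and not with the other, and both are given for the same commercial product. Whoever prepares the vial has to decide which figure to use and whether to dilute, and the protocol does not say.

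Two things are at stake. The first is participant safety: this is an injected drug given to healthy volunteers. The second is the meaning of the result. The intervention is one injection per period, so a later dose cannot correct a preparation error. If every active vial were prepared alike but not at the stated dose, the within-man comparison of IL-6 with placebo would still be randomised, but it would describe a different dose from the one reported. If vials were prepared differently, the dose would vary between men.

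The weight sentence is a separate and smaller contradiction. It describes a dose calculation that the dosing sections exclude.

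**Working it through.** **Inputs**

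- Dose D = 100 mg (section 3.6.4.1).
- Labelled volume V = 1.0 ml (section 3.6.2, Figure 1).
- Concentration C1 = 100 mg/ml (section 1.4).
- Concentration C2 = 150 mg/mL (section 3.6.1, Table 2).
- Participants: 20 men, each planned to receive one anakinra and one placebo injection in a two-period crossover (sections 3.1 and 3.5.2, Table 1). Placebo is 0.9% saline (section 3.6.1).

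**Step 1. Reproduce the stated dose.** Dose = C × V. With section 1.4: 100 mg/ml × 1.0 ml = 100 mg. This agrees with section 3.6.4.1, a difference of 0%.

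**Step 2. Repeat with Table 2, used undiluted.** 150 mg/mL × 1.0 ml = 150 mg. Relative to the stated dose: 150 / 100 − 1 = 0.50, or +50%.

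**Step 3. Volume that holds the stated dose.** Volume = D / C.
- With section 1.4: 100 / 100 = 1.0 ml, equal to the labelled volume.
- With Table 2: 100 / 150 = 0.667 ml, which is 0.333 ml short of the labelled volume.

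**Step 4. Could dilution close the gap?** Arithmetically, yes: 0.667 ml at 150 mg/mL made up with 0.333 ml of diluent gives 1.0 ml containing 100 mg. This shows only that the figures could be made to agree by a step that section 3.6.4.2 does not contain.

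**Step 5. How many injections could be affected.** Planned injections: 20 men × 2 visits = 40. Active injections: 20 × 1 = 20. Saline has no drug concentration, so the question of milligrams concerns at most 20 of 40 injections, and those only under the conditions of step 2.

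**Step 6. The weight sentence.** Section 4.2.2.1 would need a mg/kg factor to be carried out. None is given, so no weight-based dose can be computed and this contradiction has no numerical size. The procedure text of the same section also states a 100 mg injection.

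**The case against.** The strongest reply is that Table 2 and the label may describe different things. Table 2 gives the composition of the drug product. The label has a field for who prepared the vial and when, and it covers active drug and placebo alike. Section 3.5.3 assigns preparation to the clinical trial unit and says that active and placebo will match in amount once prepared. On that reading 1.0 ml is a made-up volume, and multiplying it by the Table 2 concentration is not legitimate. Table 2's heading may also refer to a 100 mg unit, in which case one unit could not supply 150 mg; that is an inference from the heading. This reply stands to the extent that it makes the 150 mg figure conditional. It does not remove the conflict between sections 1.4 and 3.6.1, and it relies on a dilution step that is not written.

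A second reply is that the intended dose is hardly in doubt, since 100 mg is stated repeatedly and the weight sentence stands alone and cannot be acted on. That is fair, and it makes the weight sentence the weaker part of the point. It is still a contradiction in the text that governs dosing day.

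Three stronger readings are tempting, and the protocol does not support them:

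- **That participants would receive 150 mg.** This requires Table 2 to be the operative concentration and the product to be used undiluted. The protocol establishes neither.
- **That every injection is affected.** Half of the planned injections are saline.
- **That the placebo volume is missing, so that blinding by volume fails.** The shared label gives 1.0 ml for both, and section 3.5.3 states that the amounts will match.

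**Conclusion.** The protocol is inconsistent as written. It gives 100 mg/ml and 150 mg/mL for one product, and nothing in the preparation section connects either figure to the labelled 1.0 ml and the 100 mg dose. The possible size is 0% if the concentration in section 1.4 applies, or if a 150 mg/mL product is diluted so that 1.0 ml holds 100 mg. It is +50% if the concentration in Table 2 applies and the product is used undiluted. At most 20 of the 40 planned injections could be affected. The weight sentence in section 4.2.2.1 contradicts section 3.2.1.1, but its effect cannot be quantified.

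These figures concern the trial's only intervention and the safety of healthy volunteers, so they should be settled before any kit is prepared. This review takes no position on which concentration, volume or dosing rule is right.

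**What to change.** The sponsor and the pharmacy should reconcile sections 1.4, 3.2.1.1, 3.6.1 (Table 2), 3.6.2 (Figure 1), 3.6.4.1, 3.6.4.2 and 4.2.2.1 so that:

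1. one concentration is stated for the product as acquired;
2. section 3.6.4.2 states the volume to withdraw and any dilution step, or states that there is none;
3. the concentration of the prepared vial multiplied by the labelled volume equals the stated dose;
4. the weight sentence for Visit 1 and the dosing sections say the same thing.

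The cost is a few lines of protocol wording and a check of the label, with a reprint only if the labelled volume changes. No change to the design, sample size or analysis follows from it.
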